## Abstract

**Introduction:**

The Qu-shi-hua-tan decoction (QSHTD), formulated by academician [name], is an empirical decoction for coronary heart disease (CHD). We conducted a randomized controlled trial to assess the effectiveness and safety of QSHTD in managing angina after coronary revascularization (AACR) in CHD patients.

**Methods and design:**

This double-blind randomized controlled trial will be conducted at Guangdong Provincial Hospital of Traditional Chinese Medicine. We will allocate 98 qualified participants to either the experimental or control group in a 1:1 ratio through random selection. The experimental group will be given standard care along with QSHTD, whereas the control group will receive standard care and a placebo. The study will span 26 weeks, consisting of a 2-week initial phase, a 12-week intervention phase, and a 12-week monitoring phase. The main outcome measure will be myocardial blood flow (MBF) assessed using adenosine stress real-time myocardial perfusion echocardiography (RTMPE). The secondary outcomes will be Canadian Cardiovascular Sociation Classification, Seattle Angina Questionnaire, Traditional Chinese Medicine (TCM) symptom evaluation; and major adverse cardiac events (MACE).

**Discussion:**

This study seeks to deliver compelling proof of the superior methodological and reporting standards of QSHTD's effectiveness and safety within AACR treatment.

**Clinical Trial Registration:**

Chinese Clinical Trial Registration Center [www.chictr.org.cn]. The trial was registered on November 26, 2020 [ChiCTR2000040270].

## Introduction

1

Coronary heart disease (CHD) is a disease of vessel stenosis or occlusion due to coronary artery atherosclerosis. CHD can lead to myocardial ischemia, hypoxia or myocardial cell death. Among the global population, cardiovascular disease including CHD and stroke is the leading cause of death and disability (1). At present, coronary heart disease incidence among middle-aged and young people in China is 10.2%, and among the elderly it is 27.8%, with an increasing trend year-over-year (2). The widespread application of coronary artery revascularization is crucial to the treatment of CHD, and this includes percutaneous coronary intervention (PCI) and coronary artery bypass grafting (3). However, about 20%–40% of patients will experience persistent angina after coronary revascularization (AACR), which detracts from quality of life and incurs immense financial costs (4). Currently, there is no consensus on the mechanism of AACR. Ischemic etiologies such as stent restenosis and stent thrombosis, and functional causes including coronary spasm and microvascular dysfunction, have been noted as potential factors contributing to chest pain. Additional non-ischemic causes include psychological factors, stent tension, chest diseases, and gastrointestinal disease (5).

Existing research on the pathogenesis of postoperative angina following coronary artery bypass grafting is limited, with PCI being the focus. Oxidation, proinflammatory and anti-inflammatory imbalance, antioxidant dysfunction, severe vascular stenosis, low ejection fraction, microcirculation disorders, and diabetes have all been cited as risk factors for post persistent coronary intervention angina among the elderly (6–8). According to the guidelines, drug treatments include nitrates, beta blockers, calcium channel blockers, and ranolazine. Patients who require revascularization will undergo PCI or coronary artery bypass grafting treatment. However, for restenosis after PCI, although some patients can be resolved through PCI, many still refuse to undergo PCI. Moreover, modern medicine lacks efficient treatment for patients with coronary microvascular disease and diffuse lesions in grafts or PCI involving multiple vessels (9). Therefore, AACR remains a challenge (10).

Traditional Chinese Medicine (TCM) serves as a complementary and alternative treatment approach for AACR (11). According to clinical research results (12–14), the combination of TCM and standard treatment alleviates AACR, with a decrease in efficacy score. The levels of inflammatory markers including high sensitivity C-reactive protein, tumor necrosis factor-α, and interleukin-6 are also decreased., while blood lipids and hemorheology are improved. Additionally, TCM treatment can reduce the incidence of major adverse cardiac events (MACEs) in patients with CHD after PCI within 5 years (15). Research on TCM syndrome and medication analysis for CHD has shown phlegm-dampness syndrome to be one of the most important syndromes in the progression of the disease (16, 17).

Qu-shi-hua-tan decoction (QSHTD) is formulated based on the academician [name]'s clinical experience with CHD treatment, and has been widely used to treat AACR with phlegm-dampness syndrome (18). The decoction consists of Magnolia officinalis (Hou Pu), Rhizoma atractylodis (Cang Zhu), Pericarpium citri reticulatae (Chen Pi), Rhizoma pinellinae praeparata (Ban Xia), Curcuma zedoary (E Zhu) and Acorus tatarinowii (Shi Chang Pu) (Table 1). Our team's previous research by [name] has indicated that QSHTD can improve cardiac function and reduce myocardial fibrosis in ApoE−/− mice after myocardial infarction and high-fat diet. It does this by regulating TLR4/NF-κb and Akt/HIF-1α signaling pathways (findings yet to be published). [name] utilized network pharmacology for an analysis which revealed that the small molecule compounds in QSHTD such as naringin and baicalin could stably bind to multiple gene receptors such as ESR1, AKT1 and MAPK1 (18).

**Table 1 T1:** Components of qu-shi-hua-tan-decoction.

No.	Pinyin	Chinese	Latin scientific name	Scientific name	Part and form used	Place of origin (China)
1	Hou Po	厚朴	Magnolia officinalis	Magnolia officinalis Rehd. et Wils. var. biloba Rehd. et Wils.	Dried bark, root bark, or twig bark	Sichuan
2	Cang Zhu	苍术	Rhizoma atractylodis	Atractylodes chinensis (DC.) Koidz.	Dried rhizome	Jiangsu
3	Chen Pi	陈皮	Pericarpium citri reticulatae	Citrus reticulata Blanco	Dried tangerine peel	Guangdong
4	Ban Xia	半夏	Rhizoma Pinellinae Praeparata	Pinellia ternata (Thunb.) Breit.	Dried tuber	Sichuan
5	E Zhu	莪术	Curcuma zedoary	Curcuma kwangsiensis S. G. Lee et C. F. Ling	Dried rhizome	Guangxi
6	Schi Chang Pu	石菖蒲	Acorus tatarinowii	Acorus tatarinowii Schott	Dried rhizome	Sichuan

As of this writing, there is a notable deficiency in robust clinical data utilizing endpoint outcomes and adverse effects as evaluation metrics, which raises uncertainty regarding the efficacy and safety of QSHTD. To address this gap, we have designed a single-center, double-blind, randomized placebo-controlled trial to investigate the efficacy and safety of QSHTD in managing AACR associated with phlegm-dampness syndrome.

## Methods

2

### Design

2.1

This is a prospective, randomized, double-blind, placebo-controlled trial. This trial was registered with the Chinese Clinical Trial Registry on November 26, 2020 (ChiCTR2000040270). This study was approved by the Research Ethics Committee at Guangdong Provincial Hospital of Traditional Chinese Medicine (BF2020-085-01). The trial complies with the Helsinki Declaration and the 2020 Good Clinical Practice guidelines. All 98 patients in this trial will be from Guangdong Provincial Hospital of Traditional Chinese Medicine. After they provide written informed consent, they will be randomly assigned to receive either QSHTD or a placebo. The study will consist of a 12-week intervention phase followed by a 12-week monitoring phase. A schematic representation of the study design is provided in Figure 1. The research process is listed in Table 2; it shows the recommended schedule for inclusion and follow-up as suggested by Standard Protocol Items: Recommendations for Interventional Trials (SPIRIT).

**Figure 1 F1:**
[figure not shown]
Study flowchart.

**Table 2 T2:** Study procedure table.

Study phase time	Baseline	Intervention period			Follow-up
	−2∼0 weeks	4 weeks	8 weeks	12 weeks	24 weeks
Data collection at baseline					
Informed consent	√				
Inclusion/exclusion criteria	√				
Random number	√				
Demographic data	√				
Disease condition	√				
Medical history					
Vital signs	√			√	
Physical examination	√			√	
Medication situation	√	√	√	√	√
Laboratory testing and other tests					
Blood analysis	√			√	
Urine analysis	√			√	
Fecal analysis + OB	√			√	
Biological sample	√			√	
Electrocardiogram	√			√	
Echocardiography	√			√	
RTMPE	√			√	
Efﬁciency evaluation					
TCM symptom scores	√			√	√
CCSC	√			√	√
SAQ	√			√	√
Other data					
AEs	√	√	√	√	√
SAEs	√	√	√	√	√
Compliance	√	√	√	√	√
Complications	√	√	√	√	√
Clinical end-point events	√	√	√	√	√

OB, occult blood; HCY, homocysteine; HbA1c, glycated hemoglobin; hsCRP, high sensitivity C-reactive protein; MCE, myocardial contrast echocardiography; AEs, adverse events; SAEs, serious adverse events. “√” Represents the need for implementation at this point in time.

### Participants

2.2

#### Diagnostic criteria for CHD

2.2.1

According to the 2013 ESC guidelines on the management of stable coronary artery disease, if coronary angiography results show any coronary artery stenosis exceeding 50%, the patient has CHD (19).

#### Diagnostic criteria for incomplete coronary revascularization

2.2.2

The calculation was based on the syntax score published in the *New England Journal of Medicine*, and residual syntax score (rSS) is the postoperative syntax score for the last revascularization surgery (20). rSS = 0 is defined as complete revascularization. rSS ≥ 1 is defined as incomplete coronary revascularization.

#### Diagnostic criteria for TCM

2.2.3

The subjects must meet both the 2017 clinical diagnostic criteria for phlegm-damp syndrome in CHD (21) and the diagnostic criteria for dampness syndrome (22). Two certified TCM cardiologists will separately conduct syndrome differentiation based on the established diagnostic standards for TCM differentiation (Tables 3, 4).

**Table 3 T3:** Diagnostic criteria for phlegm-damp syndrome.

Symptom type	Score	Item(s)
Main symptoms	3 points/item	1. Plump and teeth-printed tongue
		2. Greasy tongue fur
		3. Slippery tongue fur
Secondary symptoms	2 points/item	1. Oppression in chest
		2. Soft or slippery pulse
Other symptoms	1 points/item	1. Body trapped
		2. Sticky and greasy in mouth
		3. Obesity
		4. Viscous stool
		5. Distention and fullness
		6. Dim and dirty complexion
		7. Analeptic
		8. Anorexia

The diagnosis of phlegm dampness syndrome in coronary heart disease requires a cumulative score of ≥6 points on the indicators mentioned.

**Table 4 T4:** Diagnostic criteria for dampness syndrome.

Indicator type		Content
Specific indicators	Category 1	1.1 Greasy tongue
		1.2 Slippery coating
		1.3 Thick coating
	Category 2	2.1 Head heaviness as if being wrapped up
		2.2 Body heaviness
		2.3 Limb heaviness
		2.4 Limited joint motion with heavy sensation
	Category 3	3.1 Sticky stool with non-smooth bowel movement
		3.2 Sticky and greasy sensation in mouth
		3.3 Excessive morbid leucorrhea/moist scrotum
		3.4 Greasy hair
Sensitivity indicators	Items	1. Obesity
		2. Somnolence
		3. Idleness and laziness
		4. Non-smooth hidrosis
		5. Dirty face
		6. Dizziness
		7. Fullness and oppression in chest
		8. Excessive phlegm
		9. Distention and fullness in the epigastric region
		10. Lower abdominal fullness
		11. Soreness and weakness in the waist and knees
		12. Soreness in the joints and muscles
		13. Absence of thirst or thirst without desire to drink
		14. Poor appetite
		15. Loose stool
		16. Fetid mouth odor
		17. Enlarged tongue
		18. Soft pulse
		19. Slippery pulse

The diagnostic principle of dampness syndrome: If any one of the following conditions is met, dampness syndrome can be diagnosed: ① Meeting any one category of a specific indicator. ② Having three sensitivity indicator items. Note 1: Specific indicators are measured in category units; sensitivity indicators are measured in item units. Note 2: Specific indicators belonging to the same category, whether there is only one or multiple at the same time, are counted as one specific indicator of the same category.

#### Inclusion criteria

2.2.4

(1)Age range is from 18 to 80 years old.(2)PCI performed within the previous 2 years and rSS ≥ 2 points; or PCI was performed at least 2 years before and coronary angiography was performed within the previous 2 years with rSS ≥ 2 points; or PCI was performed at least 2 years before and there is untreated or unsuccessfully treated chronic total occlusion.(3)Meet the 2017 clinical diagnostic criteria for phlegm-damp syndrome in CHD, as well as the dampness syndrome diagnostic criteria.(4)Agree to undergo adenosine stress real-time myocardial perfusion echocardiography (RTMPE).(5)A signed consent form is required.

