#### Exclusion criteria

2.2.5

(1)Cardiogenic shock.(2)Severe heart failure (New York Heart Association classiﬁcation stages II–IV, or left ventricular ejection fraction ≤ 50%), or comorbid with severe valvular disease.(3)Severe liver or kidney dysfunction (serum alanine aminotransferase of at least double the normal upper limit and/or serum creatinine ≥ 265 μmol/L).(4)Patients with other vascular diseases, such as cerebrovascular disease, arteriosclerosis obliterans of the lower limbs or diabetes nephropathy.(5)Patients with active bleeding or severe hematopoietic system disease.(6)Patients with malignant tumors who are undergoing chemotherapy or radiotherapy who have not been clinically cured, or those who have been treated with special drugs for malignant tumors, or with life expectancy under 3 years.(7)Taken antibiotics within the previous 2 weeks.(8)Pregnant (or preparing to become pregnant) women, lactating women.(9)Have participated in, or are participating in, other clinical trials within the past 3 months.(10)The researcher determined that the participant was unable to finish the study or adhere to its requirements.

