### Sample size calculation

2.9

The sample size calculation will be based on the mean and standard deviation of the variation in MBF. According to the literature, the MBF variation in a conventional treatment group increased by 0.52 ± 0.72 (dB/s) after 12 weeks, while in the conventional combined TCM treatment group, MBF variation increased by 0.97 ± 0.68 (dB/s) after 12 weeks (26). After substituting the above values into PASS11 software with *α* = 0.05 and *β* = 0.20, the sample size required for each group was determined to be 39 cases. Accounting for a 20% dropout rate, this was adjusted to 49 cases per group. The two groups required a total of 98 patients.

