MBF represents the blood volume flowing through a specific cardiac mass per unit of time (ml/min/g) (36). In this study, we will use RTMPE to assess MBF. Image analysis for quantiﬁcation will be conducted with software (QLAB version 6.0; Phillips Medical System). The software will automatically determine the signal intensities (in decibels) for both the myocardial plateau and the neighboring left ventricular plateau, along with the signal intensity transfer rate (*β*; per second). The normalized myocardial acoustic intensity (An) is calculated as the ratio of the myocardial plateau signal intensity to the signal intensity of the adjacent left ventricular plateau. The product of An and *β* represents MBF (dB/s) (37). Canadian Cardiovascular Society Classification will be used to define physician-reported angina (24). The Seattle Angina Questionnaire, a patient reported functional status measure that is designed speciﬁcally for CHD, will be used to assess CHD patients' functional status (24).

Unlike previous which have entailed the use of real-time myocardial contrast-enhanced echocardiography, in our trial we used adenosine stress RTMPE. The quantiﬁcation of MBF during adenosine stress RTMPE is the primary outcome. The current noninvasive gold standard for diagnosing myocardial ischemia involves assessing MBF and coronary flow reserve using positron emission tomography. However, radionuclide imaging techniques are expensive and often unfeasible. Furthermore, there is a high correlation between myocardial acoustic contrast technology and positron emission tomography measurement of MBF (38). The main advantages of adenosine stress RTMPE are that there is no ionizing radiation, it is easy to operate, and it is cost-effective (39). In adenosine stress RTMPE, the application of quantitative analysis methods to evaluate MBF reserve in CHD patients is more accurate and has important value in guiding clinical prognosis. Abnormal MBF reserve and abnormal *β* reserve were indicators of overall and primary outcomes, such as cardiac mortality, non-fatal heart attacks, and intractable or unstable angina necessitating coronary revascularization during the same hospital stay, provided that elective coronary revascularization occurs at least 3 months after RTMPE (37).

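### Eligibility requires residual coronary lesions but does not exclude revascularisation already planned at screening, which admits avoidable variance and possible dilution in the 12-week MBF comparison

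*Protocol article*

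**What the plan says.** Section 2.2.4, criterion 2, of the protocol article gives three entry routes:

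- Route 1: "PCI performed within the previous 2 years and rSS ≥ 2 points". This sets an upper limit on time since PCI and no lower one.
- Route 2: "PCI was performed at least 2 years before and coronary angiography was performed within the previous 2 years with rSS ≥ 2 points".
- Route 3: PCI at least 2 years earlier, where "there is untreated or unsuccessfully treated chronic total occlusion".

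Section 2.2.2 states that "rSS ≥ 1 is defined as incomplete coronary revascularization", so every route selects patients with coronary disease left untreated.

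Section 2.2.5 lists ten exclusions. None names recent PCI or a planned, staged or scheduled revascularisation. The nearest is the discretionary tenth: "The researcher determined that the participant was unable to finish the study or adhere to its requirements". Recruitment covers inpatients and outpatients (2.3).

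After enrolment, the existing treatment plan is kept and changes are documented (2.6). Section 2.6.3 restricts drugs and is silent on procedures. The primary endpoint is the change in MBF on adenosine stress RTMPE after 12 weeks (2.7.1). Among revascularisations, only those of the target vessel are listed as an outcome, as a component of MACE (2.7.2). Effectiveness is analysed by intention to treat (2.10).

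**The concern.** Revascularisation is meant to change coronary flow, and MBF is a perfusion measure. A patient who has a second procedure between the baseline and 12-week scans therefore contributes an MBF change that mixes the procedure with the study treatment. The criteria require residual lesions, so such procedures are foreseeable. The Introduction describes guideline care in the same sense: "Patients who require revascularization will undergo PCI or coronary artery bypass grafting treatment". Section 2.6.3 also closes off most escalation of anti-anginal drugs, which leaves a procedure as one of the remaining responses to persistent symptoms.

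Two consequences are at stake. If procedures are equally common in both arms, the spread of MBF change grows and power falls. If QSHTD relieves symptoms and placebo patients go on to more procedures, placebo MBF rises for a reason other than study treatment and the arm difference shrinks. Recovery after a very recent PCI, possible only under route 1, adds variance in the same way.

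**Working it through.** **1. The plan's own sample size.** The inputs in 2.9 are: "MBF variation in a conventional treatment group increased by 0.52 ± 0.72 (dB/s) after 12 weeks"; 0.97 ± 0.68 with added TCM; α = 0.05; β = 0.20; 20% dropout.

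- Difference: 0.97 − 0.52 = 0.45.
- Pooled variance: (0.72² + 0.68²)/2 = (0.5184 + 0.4624)/2 = 0.4904; SD 0.700.
- Two-sided α = 0.05 and 80% power give 39 per group. Power from the noncentral t distribution (76 df, noncentrality 0.45/[0.700 × √(2/39)]) is 0.800; the normal approximation gives 0.810.
- 39/0.8 = 48.75, rounded up to 49 per group and 98 in total.

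The stated 39, 49 and 98 reproduce. At 39 evaluable patients per group the power is exactly at target, with no reserve.

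**2. Equal rates in both arms.** Suppose a fraction p of each arm has an extra MBF change D from a procedure or from recovery. The documents give neither p nor D; both are assumptions. The expected arm difference stays at 0.45, and the SD becomes √(0.4904 + p(1 − p)D²).

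| p | D (dB/s) | Added variance | SD | Power, noncentral t | Power, normal approx. |
|---|---|---|---|---|---|
| 0 | – | 0 | 0.700 | 0.80 | 0.81 |
| 5% | 0.5 | 0.012 | 0.709 | 0.79 | 0.80 |
| 10% | 0.5 | 0.023 | 0.716 | 0.78 | 0.79 |
| 10% | 1.0 | 0.090 | 0.762 | 0.73 | 0.74 |
| 20% | 1.0 | 0.160 | 0.806 | 0.68 | 0.69 |

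**3. Unequal rates.** With fractions pC on placebo and pT on QSHTD, the expected difference is 0.45 − (pC − pT)D, and the SD is √(0.4904 + D²[pC(1 − pC) + pT(1 − pT)]/2). For 15% on placebo against 5% on QSHTD, the bracket divided by 2 is (0.1275 + 0.0475)/2 = 0.0875.

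- D = 0.5: difference 0.45 − 0.10 × 0.5 = 0.40; SD √(0.4904 + 0.0219) = 0.716; power 0.68 (noncentral t) or 0.69 (normal).
- D = 1.0: difference 0.45 − 0.10 × 1.0 = 0.35; SD √(0.4904 + 0.0875) = 0.760; power 0.52 or 0.53.

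**4. Type I error.** In 40,000 simulated trials per setting, with 39 per arm, no QSHTD effect and equal rates, the two-sided t-test rejected in 4.9% (p = 20%, D = 1.0) and 5.0% (p = 30%, D = 1.5).

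**5. Chance imbalance.** If 20% of patients had a recent PCI, the SD of the between-arm difference in that proportion is √(2 × 0.20 × 0.80/39) = 0.091, or about 9 percentage points. This is symmetric between the arms and can be reduced by covariate adjustment.

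**The case against.** The strongest defence is the design. The trial is randomised, double-blind and placebo-controlled. Time since PCI, and any procedure already scheduled, are fixed before allocation and balanced in expectation. A reader might infer that a positive result could reflect a procedure or post-PCI recovery and not QSHTD. The documents do not support that: what both arms share cancels in the contrast, and type I error holds. The contrast moves only if procedures after randomisation differ between arms. Under blinding that would favour QSHTD only if they were commoner on QSHTD, and nothing in the documents suggests this.

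Three other tempting arguments also fail:

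- The assumed control-arm rise of 0.52 exceeds the 0.45 sought. Section 2.9 attributes that rise to conventional treatment and does not link it to procedures; a change common to both arms is subtracted.
- The Discussion's clause "provided that elective coronary revascularization occurs at least 3 months after RTMPE" might seem to support a 3-month gap between PCI and the baseline scan. It concerns revascularisation after RTMPE, within a description of prognostic outcomes, and says nothing about an interval before baseline.
- The missing minimum interval affects only route 1. Routes 2 and 3 require PCI at least 2 years earlier.

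Further points stand in part. The documents do not say that staged procedures are common in this population, and the Introduction notes that many patients with restenosis decline further PCI. Treatment changes are documented, and Table 2 records clinical end-point events at every visit. The tenth exclusion could be used against a patient with a scheduled procedure, but does not mention one. How MBF after a procedure enters the analysis is ordinary SAP content; the SAP is not shown, so its absence from the article is no fault. The printed eligibility list, however, is given in full as numbered criteria, and the gap there is a feature of the stated plan.

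**Conclusion.** The point holds as a design improvement of limited scope. The criteria select residual lesions and leave already planned revascularisation unaddressed, so the plan admits a foreseeable and avoidable source of variance in its only primary endpoint. If procedures turn out commoner on placebo, it also admits dilution toward no effect.

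The size depends wholly on assumed rates and effects. At 5% affected and 0.5 dB/s the loss of power is about one percentage point. At 10% and 1.0 dB/s it is about seven points, from 0.80 to 0.73 on the noncentral t scale (0.81 to 0.74 on the normal). With 15% against 5%, the planned difference loses 0.05 to 0.10 dB/s, or 11% to 22% of 0.45.

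The stated sample size is correct and needs no change on this account.

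**What to change.** 1. Add to 2.2.5 an exclusion for coronary revascularisation already planned or scheduled at screening to take place before the 12-week RTMPE.
2. Record time since last PCI at baseline and include it, with baseline MBF, as a covariate in the primary analysis.
3. Where the SAP does not already do so, add a sensitivity analysis of the primary endpoint for patients whose 12-week MBF was measured after an unplanned procedure.

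The first item removes the foreseeable cases. It cannot prevent unplanned, symptom-driven procedures, which are the main route to unequal rates; the third item shows how much those matter. Whether a minimum interval after PCI is needed, and how long, is a clinical decision for the investigators, and none is proposed here.

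The cost is one added eligibility line by amendment, one recorded baseline variable, some analysis text and a slightly smaller recruitment pool. No extra patients or scans are required.
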